#### Secondary outcome measurements

Body weight, body fat mass, and muscle mass will be measured by bioelectrical impedance analysis using a body composition analyzer (InBody 720, InBody Co., Ltd., Seoul, Korea) and waist and hip circumference will be measured three times by the same observer according to the World Health Organization (WHO) method [23], midpoint between the lower end of the rib cage and top of the iliac crest in a standing position, which is usually 3 cm above the anterior superior iliac spine and the widest portion of the buttocks at baseline, at 2, 3, 4, 5, and 6 weeks and endpoint (visits 2, 4, 6, 8, 10, 12, 14).

Serum metabolic profile including the following will be determined: phospholipids, fatty acids, valine, tyrosine, leucine, glycine, alanine, glutamic acid, histidine, pipecolic acid, L-carnitine, acetylcarnitine, propionylcarnitine, butyrylcarnitine, isovalerylcarnitine, hexanoylcarnitine, ocatanoylcarnitine, decanoylcarnitine, dodecanoylcarnitine, tetradeconoylcarnitine, hexadecanoylcarnitine, and octadecanoylcarnitine. Glucose, hs-CRP, and insulin will also be measured (visits 2, 14).

The International Physical Activity Questionnaire (IPAQ) [24] will be used to estimate physical activities at baseline and endpoint (visits 2, 14). IPAQ is a seven-item instrument consisting of six questions that participants answer to record the number of days (frequency) and the number of minutes per day (duration) of their participation in all types of vigorous or moderate physical activities including walking during the last 7 days. In addition, the seventh question relates to the time that participants spend sitting during an average weekday. IPAQ is considered a reasonably valid measurement tool for measuring habitual physical activities based on a recent meta-analysis [25].

The Social Readjustment Rating Scale (SRRS) [26] and the Stress Response Inventory (SRI) [27] will be used to assess stress response at baseline and endpoint (visits 2, 14). SRRS is a very well-known 43 life events-list scale measuring stress that affects health based on a relative score. Subsequent validation has supported the links between stress and illness [28]; however, the scale has been criticized for its limited clinical utility. SRI includes emotional, somatic, cognitive, and behavioral stress responses and has a significantly high reliability and validity in clinical practice [27].

The Fatigue Severity Scale (FSS) [29] will be used to assess fatigability at baseline, 2, 3, 4, 5, and 6 weeks, and endpoint (visits 2, 4, 6, 8, 10, 12, 14). FSS is the most commonly used 9-item self-report questionnaire to measure fatigue [30] and was validated as a simple and reliable instrument to assess and quantify fatigue for clinical and research purposes [31].

The Korean version of Beck’s Depression Inventory (BDI) [32] will be used to measure depressive symptoms at baseline and endpoint (visits 2, 14). BDI is a 21-item self-administered questionnaire with each item having a 0–3 response format and a maximum theoretical score of 63. The psychometric quality of this test is very good [33].

Urine samples will be measured at baseline and endpoint (visits 2, 14). Liquid chromatography quadrupole time-of-flight mass spectrometry-based nontargeted metabolomic analysis will be conducted with urine and serum samples.

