**Methods/design:**

This ongoing study is a randomized, patient-assessor blind, two-arm parallel non-penetrating sham-controlled clinical trial. Eligible participants, premenopausal adult women (19 years of age or older) with a clinical diagnosis of obesity (body mass index of 25 kg/m^2^ or more) blinded to the treatment received, will be randomly allocated blindly into the real acupuncture treatment group (manual acupuncture plus electroacupuncture, n = 60) or the sham acupuncture control group (sham acupuncture plus placebo acupuncture without electrical stimulation, n = 60) and receive treatment two times a week for a total of 12 sessions over 6 weeks. The primary outcome measure is the serum cholesterol and triglyceride (TG) levels at baseline and endpoint. The secondary outcomes are body weight, body fat mass, muscle mass, waist and hip circumference, other serum metabolic profiles, International Physical Activity Questionnaire (IPAQ), Social Readjustment Rating Scale (SRRS), Stress Response Inventory (SRI), Fatigue Severity Scale (FSS), the Korean version of the Beck Depression Inventory (BDI), and urine metabolites. Adverse events will be assessed at every visit.

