### Statistical analysis

All analyses will be performed using SPSS for Windows (version 18.0; IBM Corp., Armonk, NY, USA) and a significance level set at 0.05 by a statistician blinded to the allocation of groups. Statistical analysis will be conducted using the principles of the intention-to-treat (ITT) [34] and the per-protocol (PP) [35] analyses. We will apply the last observation carried forward (LOCF) analysis for ITT analysis.

The two-sample *t*-test for quantitative data and the chi-square test for qualitative data will be performed to test homogeneity of the baseline characteristics between the two groups. Analysis of covariance (ANCOVA) will be used for adjustment of baseline characteristics if there is a possibility of covariance. The two-sample *t*-test will be used to compare the primary and secondary variables of the two groups between baseline and endpoint. Repeated measure analysis of variance (ANOVA) will be performed for the different time point assessments between groups and interaction between groups and observed time. A mixed model approach will also be used if necessary.

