## Discussion

So far, one clinical trial has examined the effect of acupuncture on metabolic parameters in obese patients [18], which used serum cholesterol and TG levels. Referring to the previous study, we will use serum cholesterol levels including LDL, HDL, and TG levels among serum metabolic parameters as the primary outcome measurement. We will also determine other serum metabolic profiles as secondary outcome measurements, because the main purpose of this study is to assess the efficacy of acupuncture on obesity from the perspective of metabolomics and therefore better understand the pathophysiological mechanism of obesity and acupuncture. Metabolomics is defined as a technology that aims to profile metabolite changes in response to a genetic alteration or to pathophysiological stimuli [37, 38], and it provides invaluable tools for molecular biology approaches [39]. When applied to obesity, a number of metabolic perturbations, including imbalance of glucose metabolism and dyslipidemia in key organs and blood plasma, result when one consumes a high-fat diet [7]. Thus, metabolic changes are central to obesity, and we expect that any process aimed at measuring global metabolism changes would provide good evidence for the effect of acupuncture on obesity.

We adopted a complex intervention of manual acupuncture plus electroacupuncture treatment for the real acupuncture treatment group because it is the most common approach used by KMDs in South Korea today. A review of studies on acupuncture for obesity reported that manual acupuncture and electroacupuncture are more often applied in clinical trials than auricular acupuncture and moxibustion therapy [40]. In particular, electroacupuncture was reported to decrease the serum TG, total cholesterol, and LDL cholesterol [18] and was effective on abdominal obesity [41]; thus, we decided to apply electroacupuncture on abdominal acupuncture points.

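### A blanket 0.05 per test over 25 listed serum analytes gives 1.25 expected false positives under no effect, in outcomes the article calls its main purpose

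*Protocol article*

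**What the plan says.** The Secondary outcome measurements section of the protocol article opens the panel with "Serum metabolic profile including the following will be determined: phospholipids, fatty acids, valine, tyrosine, leucine" and continues through further amino acids and the carnitines. It then adds "Glucose, hs-CRP, and insulin will also be measured". Later in the same section it states that "nontargeted metabolomic analysis will be conducted with urine and serum samples". The Abstract ends its list of secondary outcomes with "the Korean version of the Beck Depression Inventory (BDI), and urine metabolites".

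The Statistical analysis section sets one level for everything: "a significance level set at 0.05 by a statistician blinded to the allocation of groups". It also says that the two-sample t-test "will be used to compare the primary and secondary variables of the two groups between baseline and endpoint". It names no adjustment, no false discovery rate and no testing order. It plans both intention-to-treat and per-protocol analyses.

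The Discussion ranks the metabolic profile as secondary but gives as the reason for including it that "the main purpose of this study is to assess the efficacy of acupuncture on obesity from the perspective of metabolomics". Its closing paragraph promises clinical evidence of efficacy, and insight into mechanism, from metabolomic methods. The article nowhere calls these analyses exploratory.

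**The concern.** The article is not silent on how secondary variables are tested. It gives a test and a level, and the metabolites fall under both. A panel of this size, tested one analyte at a time at 0.05, is expected to produce about one nominally significant analyte even if treatment does nothing. A reader of the results could not tell such a hit from a real metabolic effect.

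For a minor secondary outcome this might be tolerable. Here the stated purpose and the promised conclusions rest on this panel, so a chance finding could be reported as evidence of efficacy or as a mechanism.

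**Working it through.** **The article's own figure.** It gives no error rate for the metabolites. Its one calculation is the sample size for triglycerides (TG), which reproduces: 2 × (1.96 + 0.84)² × 56.907² / 32.5² = 48.07, taken as 48 per group; 48 / 0.80 = 60 per group, 120 in total. Only TG is sized.

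**Count of listed analytes** (Secondary outcome measurements):
- phospholipids and fatty acids: 2 entries
- valine, tyrosine, leucine, glycine, alanine, glutamic acid, histidine and pipecolic acid: 8
- L-carnitine and its acyl forms: 12
- subtotal: 2 + 8 + 12 = 22
- glucose, hs-CRP and insulin: 3
- total: 22 + 3 = 25

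This is a minimum. The first two entries are classes rather than single compounds, and the list is introduced as not exhaustive.

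**Expected false positives if no analyte is affected:** m × 0.05.
- m = 25: 1.25
- m = 22: 1.1

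These expected counts do not depend on correlation. If some analytes are truly affected, m is the number of unaffected ones.

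**Chance of at least one false positive, independent tests:** 1 − 0.95^m.
- m = 25: 1 − 0.95²⁵ = 0.723
- m = 22: 1 − 0.95²² = 0.676

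**The same chance for 25 analytes with correlated test statistics** (simulated; the article gives no correlations, so these are assumptions):

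| Assumed correlation | All 25 equally correlated | Blocks of 8 amino acids and 12 carnitines, other 5 independent |
|---|---|---|
| 0.3 | 0.60 | 0.67 |
| 0.5 | 0.46 | 0.61 |
| 0.7 | 0.32 | 0.52 |

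**How many tests make a false positive near certain?** With independent tests, ln(0.05)/ln(0.95) = 58.4, so 59 tests for 95%; ln(0.01)/ln(0.95) = 89.8, so 90 tests for 99%. The 25 listed analytes reach neither.

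**Nontargeted features, if each were tested at 0.05** (counts assumed; none are given):

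| Assumed features | Expected false positives | Chance of at least one, independent | Chance at equal correlation 0.5 |
|---|---|---|---|
| 100 | 5 | 0.994 | about 0.78 |
| 500 | 25 | above 0.999 | about 0.99 |
| 1,000 | 50 | about 1 | about 1.00 |

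**Why not Bonferroni.** Over 25 analytes the level would be 0.05/25 = 0.002. For an effect of the standardized size assumed for TG (32.5/56.907 = 0.571), with 48 evaluable per group, power would fall from 0.80 to 0.385. Restoring 0.80 would need about 95 evaluable per group.

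**The case against.** The strongest reply is that this is an omission rather than an error. A journal article condenses the full protocol, multiplicity rules for secondary omics data usually sit in the analysis plan, and that plan is not shown. A level of 0.05 can also be read as compatible with a 5% false discovery rate. This has weight: the absence of a named correction is not in itself a mistake. It does not dispose of the point, because the article states a level for all analyses and a per-variable test for the secondary outcomes. That rule, taken as written, has no multiplicity control.

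A second reply is that the metabolites are secondary, that no success criterion depends on them, and that the sample size rests on TG alone. All of this is true. A reader might infer from the main-purpose clause that the metabolomic results are confirmatory; the article does not say so. But nor does it call them exploratory, and its conclusion leans on them for efficacy and mechanism.

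A reader might also infer that false metabolomic findings are near certain. The document does not support that for the analytes it lists. The figure is about 72% under independence, which is the least plausible case when 12 of the 25 belong to one family, and it falls with correlation. Near certainty requires that every nontargeted feature be tested at 0.05. The article gives no feature count and no test specific to features; only its general rule could cover them. That part of the objection stands, and the nontargeted figures above are conditional.

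**Conclusion.** The point holds as a cheap improvement. The stated rule gives 1.25 expected false positives among the 25 listed analytes if none is affected. The chance of at least one is up to about 72%, and roughly 32% to 67% under assumed correlations of 0.3 to 0.7. All of these chances are far above 5%. The count and arithmetic come from the article; the correlations and any nontargeted feature count are assumptions. The consequence is limited to the metabolomic conclusions, but those are what the Discussion presents as the main purpose.

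**What to change.** In the Statistical analysis section, replace the blanket 0.05 for metabolomic outcomes with Benjamini-Hochberg false discovery rate control at 5%, applied within the targeted serum panel and separately within each nontargeted feature set (urine, serum). For the 25 analytes, this means ordering the p-values and declaring all those up to the largest k for which the k-th is at most (k/25) × 0.05. Report q-values, label the metabolomic results exploratory, and word the Discussion's efficacy and mechanism statements to match.

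Limit this change to the metabolomic outcomes. It should not be phrased as reserving 0.05 for one primary outcome, because the Primary outcome measurement section names HDL cholesterol, LDL cholesterol and TG.

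The cost is a few sentences in the plan and a few lines of code, with no change to data collection or sample size. The downside is that fewer metabolites will be called significant.

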#### Other assessment measures

The validated Korean version of the credibility test, which was first proposed by Vincent [21], will be used to assess the credibility of real and sham acupuncture treatments at endpoint (visit 14).

An overview of the outcome measurement time points is presented in Table 1.

**Table 1 Tab1:** Schedule for data collection, treatments, and outcome measurements

Period	S	T												F
Visit	1	2	3	4	5	6	7	8	9	10	11	12	13	14
Week	0	1^a^	1	2	2	3	3	4	4	5	5	6	6^b^	7^c^
Eligibility test	○													
Informed consent	○													
Demographic characteristics	○													
Random allocation		○												
Treatment		○	○	○	○	○	○	○	○	○	○	○	○	
Serum metabolites		○												○
BIA		○		○		○		○		○		○		○
WC/HC		○		○		○		○		○		○		○
IPAQ		○												○
SRRS		○												○
SRI		○												○
FSS		○		○		○		○		○		○		○
BDI		○												○
Urine metabolites		○												○
Adverse events		○	○	○	○	○	○	○	○	○	○	○	○	○
Credibility test														○

*S* screening period, *T* treatment period, *F* follow-up period, *BIA* bioelectrical impedance analysis, *WC* waist circumference, *HC* hip circumference, *IPAQ* International Physical Activity Questionnaire, *SRRS* Social Readjustment Rating Scale, *SRI* Stress Response Inventory, *FSS* Fatigue Severity Scale, *BDI* Beck’s Depression Inventory

^a^ Baseline (immediately before the first treatment); ^b^ end of 6-week treatment; ^c^ endpoint (within 3 days after completion of the 6-week treatment)

### Sample size

The following hypotheses are related to the differences between the treatment and control groups:$$ {H}_0:{\upmu}_{\mathrm{c}}={\upmu}_{\mathrm{t}} $$$$ {H}_1:{\upmu}_{\mathrm{c}}\ne {\upmu}_{\mathrm{t}} $$

where μ_t_ is the mean TG level in the real acupuncture treatment group and μ_c_ is the mean TG level in the sham acupuncture control group at endpoint.

Referring to a previous study [18], the researchers expect the mean difference will be 32.5 with a standard deviation of 56.907 between the two groups.

For the mean comparison method of the two-sample *t*-test model, this study will use a level of significance of α = 0.05 and a power of 1-β = 0.80 and the following two-sided test:$$ N=\frac{2\times {\left({\mathrm{Z}}_{\upalpha}+{\mathrm{Z}}_{\upbeta}\right)}^2\times {\upsigma}^2}{\updelta^2}=\frac{2\times {\left(1.96+0.84\right)}^2\times {56.907}^2}{32.5^2}=48.07\approx 48 $$

For equal allocation of the two groups, the total sample size required when considering a dropout rate of 20 % is 120 subjects with 60 subjects in each group.

### Statistical analysis

All analyses will be performed using SPSS for Windows (version 18.0; IBM Corp., Armonk, NY, USA) and a significance level set at 0.05 by a statistician blinded to the allocation of groups. Statistical analysis will be conducted using the principles of the intention-to-treat (ITT) [34] and the per-protocol (PP) [35] analyses. We will apply the last observation carried forward (LOCF) analysis for ITT analysis.

The two-sample *t*-test for quantitative data and the chi-square test for qualitative data will be performed to test homogeneity of the baseline characteristics between the two groups. Analysis of covariance (ANCOVA) will be used for adjustment of baseline characteristics if there is a possibility of covariance. The two-sample *t*-test will be used to compare the primary and secondary variables of the two groups between baseline and endpoint. Repeated measure analysis of variance (ANOVA) will be performed for the different time point assessments between groups and interaction between groups and observed time. A mixed model approach will also be used if necessary.

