### Intervention

Both real and sham acupuncture groups will receive a total of 10–12 acupuncture sessions. At the time of the first acupuncture session, all participants will be given a “dietary and exercise manual for obese patients” from the obesity clinic of the Korean Medicine Hospital of Kyung Hee University at Gangdong.

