### Outcome

#### Primary outcome measurement

The primary outcome measure is the serum cholesterol levels including HDL cholesterol, LDL cholesterol, and triglyceride (TG) levels. Peripheral blood will be drawn from the antecubital veins of the subjects in the real and sham acupuncture groups at baseline (visit 2) and endpoint (visit 14: within 3 days after completion of the 6-week treatment) after a 10–12 hour overnight fast. Blood samples will be collected in serum-separating tubes (5 mL), sodium fluoride tubes (3 mL), and EDTA-coated tubes (2 mL) and will be centrifuged at 3,000 rpm for 10 minutes to separate either serum or plasma depending on the requirement of the analysis. Aliquots of plasma and sera will be obtained, and serum-separating tubes and sodium fluoride tubes will be stored at 2 to 10 °C while EDTA-coated tubes will be stored at −80 °C for further analysis. Analysis of TG, HDL cholesterol, LDL cholesterol, free fatty acids, glucose, hs-CRP, and insulin will be performed by an outsourcing laboratory (EOne Laboratories, Incheon, South Korea), and analysis of other lipids, amino acids, and carnitines will be commissioned to the research laboratory of the College of Pharmacy, Hanyang University in Korea.

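### For the primary lipids, measured only at baseline and endpoint, the ITT rule of LOCF amounts to baseline carried forward and shrinks any true effect by the dropout fraction

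*Protocol article*

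**What the plan says.** Under Statistical analysis, the protocol article plans the work "using the principles of the intention-to-treat (ITT) [34] and the per-protocol (PP) [35] analyses" and then gives one missing-data rule: "We will apply the last observation carried forward (LOCF) analysis for ITT analysis". No outcome is exempted. The between-group test is described as follows: "The two-sample *t*-test will be used to compare the primary and secondary variables of the two groups between baseline and endpoint". A further sentence adds: "A mixed model approach will also be used if necessary". It gives no condition for using that model.

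Under Primary outcome measurement, the primary outcome is defined: "The primary outcome measure is the serum cholesterol levels including HDL cholesterol, LDL cholesterol, and triglyceride (TG) levels". Blood is drawn "at baseline (visit 2) and endpoint (visit 14: within 3 days after completion of the 6-week treatment"). Table 1 agrees: serum metabolites are marked at visits 2 and 14 and nowhere else, and its footnote places the baseline immediately before the first treatment.

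The Sample size section writes the hypothesis for mean triglyceride at endpoint, with a difference of 32.5 and an SD of 56.907. It allows for 20% dropout and arrives at 60 per arm.

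**The concern.** LOCF presumes that there is a post-baseline observation to carry. Weight, body composition, circumferences and the fatigue scale have such values at visits 4 to 12. The primary lipids have none. For a participant with no visit-14 sample, the rule inserts the value taken before any treatment, so that person enters the ITT analysis as if nothing had changed.

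Two consequences follow. First, a real effect is diluted in proportion to the share of imputed participants, and raising 48 to 60 per arm does not make up for this: that step replaces lost observations but does not restore a shrunken difference. Second, if lipids drift in both arms and dropout is unequal, the arm with more imputed zeros shows less of the common drift, and an arm difference appears that is not due to treatment. A shared drift is plausible because of this step in the Intervention section: "At the time of the first acupuncture session, all participants will be given a" diet and exercise manual. The article states no expected lipid effect of that manual.

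**Working it through.** **Inputs from the article.** Difference 32.5; SD 56.907; two-sided 0.05; power 0.80; 20% dropout; 60 per arm (Sample size). Lipids at visits 2 and 14 only (Primary outcome measurement, Table 1).

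**The plan's own figure.** 2 × (1.96 + 0.84)² × 56.907² / 32.5² = 48.07, taken as 48; 48 / 0.80 = 60 per arm. Both reproduce. The dropout allowance corresponds to 60 × 0.20 = 12 participants per arm.

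**Expected difference under the rule.** Let d_t and d_c be the fractions without a visit-14 sample in the real and sham arms, and c_t and c_c the true mean changes. Imputed participants contribute zero change and, for simplicity, dropout is taken as random within arm:

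expected difference = (1 − d_t) × c_t − (1 − d_c) × c_c

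With equal dropout d this is (1 − d) × (c_t − c_c). At d = 0.20: 0.80 × 32.5 = 26.0. At 10% it is 29.25 and at 30% it is 22.75. If c_t = c_c and d_t = d_c, it is 0.

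**Power, endpoint reading** (raw triglyceride at visit 14, two-sample t-test, 60 per arm):
- Complete data, 60 per arm, difference 32.5: 0.87.
- 48 completers per arm, difference 32.5: 0.79.
- LOCF, difference 26.0, SD kept at 56.907: SE = 56.907 × √(2/60) = 10.39; power 0.70.
- LOCF, allowing for the mixing of carried and observed values: the variance per arm becomes 56.907² + d(1 − d) × change². With no sham-arm change, the variances are 3238.4 and 3407.4, SE 10.52, power 0.69. With an assumed sham-arm fall of 20 (real-arm fall 52.5), they are 3302.4 and 3679.4, SE 10.79, power about 0.67. Simulation gave values down to 0.66.

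**Power, change reading** (56.907 taken as the SD of change; variance per arm = (1 − d)(56.907² + c²) − ((1 − d)c)²):
- No sham-arm change: variances 2590.7 and 2759.7; SE = √(5350.4/60) = 9.44; 26.0/9.44 − 1.96 = 0.79; power 0.79 (normal approximation).
- Sham-arm fall of 20: variances 2654.7 and 3031.7; SE 9.74; 26.0/9.74 − 1.96 = 0.71; power 0.76.
- The imputed zeros shrink the variance along with the mean, so the loss against 48 completers per arm is only about 0-3 points. If baseline and endpoint are highly correlated, change-score power exceeds 0.80 even under LOCF.

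**Unequal dropout** (both the dropout split and the common change are assumptions; the article gives neither):

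| True situation | Dropout real / sham | Difference estimated under LOCF |
|---|---|---|
| No effect, both arms fall 20 | 10% / 30% | 0.90 × (−20) − 0.70 × (−20) = −4.0 |
| No effect, both arms fall 20 | 30% / 10% | +4.0 |
| No effect, both arms fall 10 | 15% / 25% | 0.85 × (−10) − 0.75 × (−10) = −1.0 |
| Effect −32.5 (falls of 52.5 and 20) | 30% / 10% | 0.70 × (−52.5) − 0.90 × (−20) = −18.75 |
| Effect −32.5 (falls of 52.5 and 20) | 10% / 30% | 0.90 × (−52.5) − 0.70 × (−20) = −33.25 |

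The spurious 4.0 raises the type I error to about 6.6-8.6%, depending on the baseline-endpoint correlation and the reading of the test. The milder case leaves it at about 5.1-5.2%.

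**The case against.** The best defence is that, under the plan's own assumption of one 20% dropout rate, the rule is conservative: it pulls a true effect toward zero and creates no false positives. That stands. A reader might infer that LOCF biases the result whenever anyone drops out, or that it generally inflates type I error. The documents do not support this. A false-positive risk needs unequal dropout together with a common lipid change, and the article gives figures for neither.

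Second, the power shortfall depends on how the test is read. The hypothesis in the sample size section concerns endpoint means, but the analysis section speaks of comparing the groups between baseline and endpoint, which can naturally mean change. On that reading the loss is slight. It would therefore be too strong to say outright that the plan cannot deliver 80% power.

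Third, not every dropout is affected. Someone who stops treatment but attends visit 14 has an observed value. Nor is the sample size wrong as such: 48 / 0.80 = 60 is ordinary inflation, and the 20% is an allowance, not a forecast.

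Fourth, a per-protocol analysis and a mixed model are mentioned. Neither repairs the ITT result as written. The per-protocol analysis addresses a different set of participants, and the mixed model has no stated trigger and does not replace LOCF.

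Finally, one might leave the matter to a statistical analysis plan that is not shown. But this is not an omitted detail: the article names the rule, and the rule does not fit the schedule of the primary outcome.

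**Conclusion.** The point holds in this form. For any participant without a visit-14 sample, the stated ITT rule sets the primary lipids to their pre-treatment value. Relative to the effect that would have been seen had everyone been measured, a true difference is attenuated by the dropout fraction when dropout is equal and random: 32.5 to 26.0 at the planned 20%, a loss of 6.5. The attenuation of the estimate is the same whether endpoint or change is tested; the power loss is not, running from about 9-13 points below 48 completers per arm on the endpoint reading to about 0-3 points on the change reading. There would be no attenuation if the lipids of those who leave truly stayed at baseline on average, but the article gives no reason to expect that.

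With unequal dropout and a common change, the estimate can be too small or slightly too large. The figures of 4.0, 18.75 and 33.25 illustrate this under assumed inputs and are not predictions for this trial. Because the rule bears on the ITT estimate of the primary outcome, it should be changed before unblinding.

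**What to change.** For the primary lipids and the other outcomes measured only at visits 2 and 14, replace LOCF as the main ITT method by one of the following:

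- a likelihood-based model of the baseline and visit-14 values; or
- multiple imputation by arm, using baseline lipids and the weight, body-fat and waist values already collected at visits 4, 6, 8, 10 and 12.

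Name the chosen method as the main ITT analysis instead of leaving a mixed model to need. Keep baseline carried forward as a sensitivity analysis under that name, and report the number of missing visit-14 samples by arm.

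The change costs some wording and a little more programming; it needs no new visits, samples or participants. The drawback is reliance on a missing-at-random assumption, which the data cannot confirm and which the sensitivity analysis should probe.

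### The primary triglyceride comparison is an unadjusted t-test with ANCOVA held back for an undefined trigger; fixing ANCOVA on baseline triglyceride would cost nothing and be more precise

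*Protocol article*

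**What the plan says.** Three statements in the protocol article bear on this.

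- **Statistical analysis, adjustment.** Baseline homogeneity is to be tested by t-test and chi-square test. The next sentence reads "Analysis of covariance (ANCOVA) will be used for adjustment of baseline characteristics if there is a possibility of covariance". It gives no criterion and names no covariate.
- **Statistical analysis, main comparison.** The two-sample t-test "will be used to compare the primary and secondary variables of the two groups between baseline and endpoint".
- **Sample size.** The hypotheses concern endpoint means; the control-group parameter "is the mean TG level in the sham acupuncture control group at endpoint". The assumptions are that "the researchers expect the mean difference will be 32.5 with a standard deviation of 56.907 between the two groups", under a two-sample t-test with no covariate.

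Under Primary outcome measurement and in Table 1, fasting blood for TG is drawn at visit 2 (baseline) and visit 14 (endpoint). Baseline TG is therefore planned for every participant.

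**The concern.** In a randomised trial any baseline difference between arms is due to chance, so a test of baseline homogeneity is no sound basis for choosing the outcome model. Baseline TG deserves adjustment because it is expected to predict endpoint TG, and that can be decided now. The protocol instead leaves adjustment to an undefined condition which, from its position straight after the homogeneity tests, is probably linked to them.

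Two things are at stake. First, an open condition leaves two candidate primary p-values, one adjusted and one not. Second, endpoint values and change scores have different standard deviations, linked by the baseline-endpoint correlation. If the analysis is of change and the sample size is for endpoint means, the stated power need not apply.

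**Working it through.** **Inputs (Sample size section).** Difference δ = 32.5, SD = 56.907, two-sided α = 0.05, planned power 0.80, 1:1 allocation, 20% dropout. The correlation ρ between baseline and endpoint TG is not given; 0.3, 0.5 and 0.7 are assumptions.

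**The plan's own figure.** n = 2(1.96 + 0.84)² × 56.907² / 32.5² = 15.68 × 3238.4 / 1056.25 = 48.07, taken as 48 per arm. Then 48 / (1 − 0.20) = 60 per arm, 120 in total. This reproduces the protocol. Unrounded normal quantiles give 48.13.

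**Power of the endpoint t-test at 48 per arm.** Standard error = 56.907 × √(2/48) = 11.62; noncentrality = 32.5 / 11.62 = 2.80; power from the noncentral t with 94 degrees of freedom = 79%.

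**Case A: 56.907 is the endpoint SD, equal at baseline.**

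- SD of change = 56.907 × √(2(1 − ρ))
- ANCOVA residual SD = 56.907 × √(1 − ρ²), with 93 degrees of freedom

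| ρ (assumed) | SD of change | ANCOVA SD | Power, change t-test | Power, endpoint t-test | Power, ANCOVA |
|---|---|---|---|---|---|
| 0.3 | 67.3 | 54.3 | 65% | 79% | 83% |
| 0.5 | 56.9 | 49.3 | 79% | 79% | 89% |
| 0.7 | 44.1 | 40.6 | 95% | 79% | 97% |

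The change SD equals the endpoint SD when 2(1 − ρ) = 1, that is, at ρ = 0.5. Below that the change test is weaker than planned; above it, stronger.

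**Case B: 56.907 is the SD of change.** The change t-test has 79% power by construction. The ANCOVA SD is 56.907 × √((1 + ρ)/2) = 45.9 / 49.3 / 52.5, giving 93 / 89 / 85% at ρ = 0.3 / 0.5 / 0.7. An endpoint test would have SD 56.907 / √(2(1 − ρ)) = 48.1 / 56.9 / 73.5 and power 91 / 79 / 57%. That last combination takes the less natural reading of both sections, but it too shows why test and SD must be of the same kind.

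**Type I error (simulation, 48 per arm, 40,000 runs, normal data, Case A).**

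| Rule | ρ = 0.3 | ρ = 0.5 | ρ = 0.7 |
|---|---|---|---|
| ANCOVA if baseline TG differs at p < 0.05, otherwise change t-test | 4.0% | 4.2% | 4.5% |
| Same, otherwise endpoint t-test | 4.8% | 4.2% | 3.6% |
| Whichever of change t-test and ANCOVA is significant | 7.8% | 7.1% | 6.7% |

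The first rule has power of 66 / 80 / 95%, close to the change test alone, so it loses most of what ANCOVA would gain.

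**The case against.** The strongest reply is that the wording is loose and the harsher readings are inferences.

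- **A reader might infer that adjustment depends on a significant baseline test.** The text does not say so. The homogeneity tests are in a separate sentence and no p-value threshold is given. What stands is that the condition is undefined on any reading.
- **A reader might infer that the primary test is definitely of change and the trial therefore underpowered.** No change score is mentioned, and the Sample size section speaks of endpoint means, so an endpoint t-test is possible. In that case, with 56.907 as the endpoint SD, the mismatch disappears and power is 79%, essentially as planned. If the test is of change, power exceeds plan once the correlation is above about 0.5.
- **A reader might infer that the conditional rule inflates type I error.** A strictly applied baseline-test trigger does not: the simulated error is 3.6 to 4.8%. The 6.7 to 7.8% needs an analyst to report whichever test is significant, which the protocol does not plan. Blinding the statistician to allocation limits steering towards one arm, although it does not prevent selection by p-value.
- **Model detail belongs in an analysis plan.** That is true of omissions. Here the protocol itself states a conditional choice of model and a test that does not clearly match its sample size hypothesis.

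It also stands that an unadjusted two-sample t-test is valid and unbiased under 1:1 randomisation, and that the sample size arithmetic is sound.

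**Conclusion.** The point holds as a should-fix. The protocol fixes the less efficient analysis as its stated comparison, leaves the route to the better one undefined, and does not clearly analyse the quantity on which it was sized.

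ANCOVA on baseline TG is at least as powerful as the t-test under every reading, apart from one degree of freedom. At 48 per arm its gain over the change test is 18, 10 and 2 percentage points at correlation 0.3, 0.5 and 0.7 if 56.907 is the endpoint SD, and 14, 10 and 6 points if it is the SD of change. Against an endpoint test, with the endpoint SD, it is 4, 10 and 18 points.

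With the endpoint SD that the Sample size section implies, the planned 80% is materially missed only by a change test with correlation below about 0.5. These sizes rest on the assumed correlations, equal SDs at the two visits and roughly normal data. The findings do not show that the trial is underpowered or that its error rate is uncontrolled.

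**What to change.** 1. State that the primary TG analysis is ANCOVA of visit-14 TG on treatment group with visit-2 TG as covariate, used whatever the baseline comparisons show, and report the adjusted difference with its 95% confidence interval.
2. Do not use baseline significance tests to choose the model; a descriptive baseline table is enough.
3. Align the Sample size and Statistical analysis sections on one quantity, and say whether 56.907 is an SD of endpoint values or of change.
4. Use the same approach for the other continuous outcomes measured at visits 2 and 14.

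The cost is a change of wording, made before unblinding, and one degree of freedom. Baseline TG is already collected, and the 120 participants need not change.
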